In Singapore, we found that participants who consumed mushrooms >2 portions per week had 47% reduced odds of having MCI (Feng et al., 2019). The association between mushroom consumption and MCI may be mediated by interleukin-6 and hypersensitive C-reactive protein (Chen et al., 2024). Those with higher mushroom consumption were also found to have better cognitive performance as assessed by the Digit Symbol Substitution test (DSST)(Ba et al., 2022; Yan et al., 2023; Nurk et al., 2010), Trail Making Test (TMT)(Yan et al., 2023), block design (Nurk et al., 2010), and the Word Learning test (CERAD-WL)(Ba et al., 2022). In an 18-year prospective study in the UK, mushroom consumers were found to have better cognitive performance than non-consumers across multiple cognitive domains. The relationship was observed to be dose-dependent, with those consuming one or more portions per week showing the highest cognitive score (Cha et al., 2024).

However, observational data do not prove causality, prompting five RCTs (3 weeks–6 months; *n* = 30–436), mostly using ergothioneine-rich Hericium erinaceus (HE), which have yielded mixed results: 3 g/day HE for 16 weeks modestly improved MCI cognition (reversed after a 4-week washout) (Mori et al., 2009), and 1.05 g/day for 49 weeks improved MMSE in AD patients (Saitsu et al., 2019), yet higher doses in healthy adults and a 436-subject, 24-week Australian trial showed no benefit (Zajac et al., 2020). Heterogeneity in species, cultivation, dosing, and duration complicates interpretation and generalization.

Mushrooms contain bioactive compounds such as ergothioneine, which has demonstrated antioxidant and neuroprotective effects in cell and animal models (Cheah and Halliwell, 2021; Tang et al., 2018; Cheah and Halliwell, 2012; Wu et al., 2021; Cheah et al., 2016; Wu et al., 2022; Halliwell and Cheah, 2024). However, human data on ergothioneine’s cognitive benefits remain limited. Accordingly, our trial is designed to explore both clinical outcomes and underlying biological mechanisms—such as changes in plasma ergothioneine levels, inflammatory markers, and DNA methylation profiles—rather than to confirm a definitive neuroprotective effect (Figure. 1).

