### Randomized controlled trial

3.2

We will conduct a randomized, controlled trial to assess the effects of mushroom powders on cognitive function and epigenetic and inflammatory markers of aging. There will be a total of 600 participants: 300 in the mushroom powder intervention arm and 300 in the placebo control arm. An interim assessment will be conducted when the sample size reaches 200 participants. Trial participants will be screened from two community-based observational cohort studies in Singapore [the DaHA (Chan et al., 2018) study and the Aging in a Community Environment Study (ACES) (Liew et al., 2018)], one completed RCT [the Choral Singing RCT (CSRCT)], and open recruitment via newspaper and poster advertisement at community centers, as well as advertisement on social media and websites. The above three studies led by the applicant have successfully recruited and assessed over 1,500 subjects. The mean age of DaHA, ACES and CSRCT participants in 2025 are projected to be 78, 80 and 79 years, respectively. Given the 20.7-year life expectancy at age 65 in Singapore. We estimate that at least 83% of them would be alive when the trial starts. All subjects have had comprehensive cognitive assessment and most of them have consented to be contacted for future research. Once eligible subjects from the two cohort studies are enrolled in the proposed RCT, they will no longer be considered part of the observational cohorts. No further follow-up visits will be conducted on these participants according to the DaHA-ACES cohort protocol, ensuring that the validity of findings from the cohort studies is not affected. This will be clearly communicated to trial participants selected from the cohorts. Our inclusion criteria are: (1) Community-living adult aged 45 years to 74 years. (2) Family history of Alzheimer’s disease or other types of dementia or carrying at least one *APOE* ε4 allele or having subjective cognitive (SCD) defined as “self-reported memory problems that have been getting worse over the past year.” (3) Consume mushrooms no more than once a week. (4) No dementia: CDR global score equal to zero. Exclusion criteria are: (1) Any diagnosis of neurological diseases (e.g., epilepsy, stroke) made by a clinician. (2) Any diagnosis of psychiatric illnesses (e.g., depressive disorders) made by a clinician. (3) Marked hearing impairment, visual impairment or upper limbs motor difficulties that make the person unable to complete cognitive assessment.

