
**Table 1 tab1:** Measurements and visit schedules.

S.no.	Measurement	Baseline	1 year	2 years
1	Socio-demographics	√		√
2	Lifestyles, dietary intake (FFQ)	√	√	√
3	Medical conditions, medications, supplements	√	√	√
4	Mini mental state examination (MMSE)	√	√	√
5	GDS-15 or PHQ-9 for depressive symptoms	√	√	√
6	Neuropsychological tests (3 cognitive tests as a battery)	√	√	√
7	Clinical dementia rating (CDR)	√	√	√
8	Handgrip strength, repeated chair rise test, blood pressure	√	√	√
9	Venous blood sample collection and blood-based biomarkers	√		√

For cognitive measures, we selected locally validated and normed tools to ensure sensitivity to changes over time. We have carefully considered and included a panel of biological markers based on potential pathways. We will measure pro-inflammatory cytokines (such as hs-CRP, TNFα, IL-1, IL-6, etc.), and neurofilament light chain (NfL) as a non-specific biomarker of neurodegeneration (AD). We will also measure the genetic polymorphism of *APOE* gene and the DNA methylation profile. This biological approach has a clear advantage over traditional trials that only assess clinical outcomes and clinical laboratory tests.

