### Methods of analysis

3.5

To test the relationship between mushroom consumption and cognition among cohort participants: A linear regression model will be used to assess how baseline mushroom consumption predicts future cognitive changes. A log-binomial regression model will be used to compare the proportion of incidental cognitive impairment cases in the subgroups defined by mushroom consumption. A sensitivity analysis will be performed using a log-binomial model for repeated measures, including assessments at the 5-year follow-up and controlling for major demographic, medical, and lifestyle factors. Pre-specified subgroup analyses will stratify by baseline cognitive status (MMSE ≥ 27 vs. < 27), sex, and education level (≤ secondary vs. > secondary). Interaction terms will test for differential intervention effects.

*A priori* power calculation was performed using G*Power 3.1. Assuming a small-to-medium effect size of Cohen’s d = 0.30 in 24-month MMSE change, two-tailed *α* = 0.05 and 90% power, 235 subjects per arm are required. Allowing 20% attrition at 24 months (Jacobsen et al., 2021), we plan to enroll 300 per arm.

To test the effects of ET-Rich mushroom powder on cognitive function among RCT participants: A linear regression model will be performed to compare changes in cognitive scores at 24 months between the intervention and control arms. A sensitivity analysis will be performed using a general regression model for repeated measures, including assessments at 12 months and controlling for major demographic, medical and lifestyle factors at baseline.

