To examine the underlying protective mechanisms: The levels of biomarkers will be treated as continuous variables. Changes in biomarkers will be calculated by comparing post-intervention levels to pre-intervention levels from intervention and control and represented in percentage (%). These changes will then be compared between the intervention and control groups. Furthermore, paired two-tailed t-tests will be performed to assess whether biomarker levels differ between pre-intervention and post-intervention measurements within each group (control and intervention). To analyze the ergothioneine data, we will use a “change-versus-change’ approach, using repeated ergothioneine measurements as predictors to examine their relationship with changes in cognition and other biomarkers. We will further employ Structural Equation Modeling (SEM) to assess how the intervention affects cognitive function, with ergothioneine as a hypothesized mediating factor. In the SEM, we will adjust for age, sex, education (social class proxy), BMI, APOE ε4 status, baseline supplement use (curcumin, Ginkgo, omega-3), individual metabolic variations by including plasma liver enzymes (ALT, AST) and baseline renal function & ergothioneine levels as covariates, and compliance rate. Interaction terms will test effect modification.

To examine the epigenetic changes associated with ET-Rich mushroom consumption: Analysis of epigenome-wide methylation data will be performed using a modified version of the CPACOR pipeline(Lehne et al., 2015). Briefly, we will normalize marker intensities by quantile normalization. Single-marker tests using logistic regression will be used to examine the association of mushroom consumption with each autosomal CpG site (yes/no), adjusted for age and sex. Principal components from intensity values of Infinium control probes will also be included as covariates in the regression models. Finally, the association results will be adjusted for the genomic control inflation factor. We will subsequently develop a methylation risk score (MRS) model by taking a weighted approach (by effect size) for the CpG loci identified to be associated with mushroom consumption. Figure 3 describes the flow of study participants.

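### The mediation SEM's stated covariate list omits diet, lifestyle, medical and two entry-criterion variables that the trial collects, so the non-randomised ergothioneine-to-cognition path is open to avoidable confounding

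*Protocol article*

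**What the plan says.** Section 3.5 plans an SEM of how the intervention affects cognition, "with ergothioneine as a hypothesized mediating factor". The covariates are set out explicitly. The list opens with "we will adjust for age, sex, education (social class proxy), BMI, APOE ε4 status, baseline supplement use (curcumin, Ginkgo, omega-3"), and closes with "plasma liver enzymes (ALT, AST) and baseline renal function & ergothioneine levels as covariates, and compliance rate". Beside the SEM there is a change-against-change analysis, "using repeated ergothioneine measurements as predictors to examine their relationship with changes in cognition and other biomarkers".

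Other sections show what is collected but not on that list:

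- Table 1, row 2, has "Lifestyles, dietary intake (FFQ") at baseline, 1 year and 2 years. Row 3 has medical conditions, medications and supplements at the same visits; only supplements reach the SEM.
- Inclusion criterion 2 in section 3.2 admits a person with a family history of dementia, an APOE ε4 allele, or SCD, defined as "self-reported memory problems that have been getting worse over the past year". Only APOE ε4 is in the SEM.
- The repeated-measures sensitivity analysis of trial cognition is adjusted more widely, "controlling for major demographic, medical and lifestyle factors at baseline".

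**The concern.** Randomisation protects the effect of arm on ergothioneine and the effect of arm on cognition. It does not protect the effect of ergothioneine on cognition. Within an arm, people differ in follow-up ergothioneine because of diet, how their bodies handle the compound and, in the active arm, how much they take. Some of these sources may also bear on cognition. The Introduction itself warns that "observational data do not prove causality", and this path is observational.

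The arm-to-ergothioneine path should be clearly non-zero if the capsules deliver the compound. The indirect effect is the product of the two paths, so any bias in the second path passes straight into the reported mediation. Aim 3, and the closing paragraph of section 3.4 on ergothioneine's mediating role, would then be supported by a coefficient that partly reflects diet or general health. The plan considers medical and lifestyle factors relevant enough to cognition to adjust for elsewhere, but leaves them off the list for this path.

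**Working it through.** **1. The plan's own figure.** The article gives no number for the SEM, only the primary sample size. With d = 0.30, two-sided 5% and 90% power, the normal approximation gives 234 per arm and the noncentral t gives 235 (power 0.9007 at 235, 0.8994 at 234). Allowing for attrition, 235 / 0.80 = 293.75, so 294, planned as 300. The figure reproduces. It supplies one input: 300 × 0.80 = 240 evaluable per arm, 480 in all.

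**2. Covariates compared with data collected.**

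| Variable | Collected | In SEM list |
|---|---|---|
| Age, sex, education, BMI, APOE ε4, supplements | yes | yes |
| ALT, AST, renal function, baseline ergothioneine, compliance | yes | yes |
| FFQ diet, lifestyle | Table 1 row 2, three visits | no |
| Medical conditions, medications | Table 1 row 3, three visits | no |
| Family history, SCD | inclusion criterion 2 | no |

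**3. Closed-form size.** Assume no true ergothioneine effect and an omitted factor with within-arm correlation r1 with follow-up ergothioneine and r2 with cognitive change. The induced correlation is r = r1 × r2. With about 465 residual degrees of freedom, z = atanh(r) × √465, and the rejection probability is Φ(z − 1.96) + Φ(−z − 1.96).

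- r1 = 0.2, r2 = 0.1: r = 0.02, z = 0.43, rejection 7.2%
- r1 = 0.3, r2 = 0.15: r = 0.045, z = 0.97, rejection 16.3%
- r1 = 0.4, r2 = 0.2: r = 0.08, z = 1.73, rejection 40.9%

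A simulation of the same three cases (2,000 runs, n = 480, arm and baseline ergothioneine in the model) gave 6.8%, 16.5% and 37.0%.

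**4. Simulation with diet that changes over time.** Assumptions: diet at baseline and follow-up, D0 and D24, are standard normal with correlation s. Ergothioneine loads g on concurrent diet and also has a stable personal component. The intervention raises it by 1 SD. Cognitive change has correlation c with average diet and no dependence on ergothioneine. There are 240 per arm and 1,000 runs per row. Mediation is declared when both paths are significant at 5%.

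| s | g | c | Arm + baseline ergothioneine | + D0 | + D0 and D24 |
|---|---|---|---|---|---|
| 0.5 | 0.3 | 0.1 | 6.7% | 6.8% | 5.3% |
| 0.5 | 0.5 | 0.2 | 20.4% | 20.5% | 4.1% |
| 0.5 | 0.5 | 0.3 | 38.7% | 39.1% | 6.7% |
| 0.7 | 0.3 | 0.1 | 6.9% | 6.7% | 6.2% |
| 0.7 | 0.5 | 0.2 | 18.4% | 10.7% | 4.6% |
| 0.7 | 0.5 | 0.3 | 39.8% | 21.4% | 5.5% |

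Over the whole grid (g 0.3 or 0.5; c 0.1 to 0.3), the model with baseline ergothioneine falsely declares mediation in about 7% to 40% of trials, with a spurious indirect effect of about 0.02 to 0.09 SD. Without baseline ergothioneine the range is about 10% to 86%, so that covariate does real work: it removes about a third of the bias.

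Adding baseline diet helps at s = 0.7 and hardly at all at s = 0.5. The last column is near nominal because simulated diet is measured without error. A real FFQ would achieve less.

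**The case against.** Much can be said for the plan as written. The list is not thin: BMI, supplements, liver enzymes and renal function address individual handling of the compound, and baseline ergothioneine is a partial proxy for habitual mushroom intake. Entry is limited to people who eat mushrooms no more than once a week, which narrows the main dietary source at baseline in both arms. The Introduction says that mechanisms are to be explored rather than a neuroprotective effect confirmed, and section 3.5 also compares biomarker changes between the randomised arms. A full analysis plan might add covariates, and no list removes unmeasured confounding.

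All of this limits the size and stakes of the point. It does not remove the point, because the article states an explicit list that can be judged as written, and the omitted variables are already collected.

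Some stronger readings are tempting but unsupported:

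- A reader might infer that the plan adjusts for medical and lifestyle factors only where randomisation makes it unnecessary. It does not: the cohort's log-binomial sensitivity analysis in section 3.5 is adjusted for them too.
- A reader might infer that listing APOE ε4 without the other entry criteria spoils an APOE interaction test. The plan says only that interaction terms will test effect modification and does not name an APOE term. Any figure would need prevalences that the document does not give.
- A reader might infer that the entry criteria are all left out; APOE ε4 is in the list.
- A reader might infer that any mediation found would be nothing but the diet-cognition association. The document gives no correlation from which to conclude that.

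**Conclusion.** The point holds in a limited form. The stated SEM list leaves out collected variables that could plausibly confound the ergothioneine-to-cognition path, and the existing covariates and the entry limit on mushrooms reduce the problem without removing it. False rejection at a nominal 5% runs from close to nominal (about 7%) to about 40%. That range rests wholly on assumed correlations, on 480 evaluable participants and on no true ergothioneine effect. It shows what could happen and does not estimate the error rate of this trial.

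The randomised primary comparison of MMSE change is untouched. The change is worth making because it protects a named, though exploratory, aim at little cost.

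**What to change.** In section 3.5, extend the SEM covariates in both the ergothioneine and the cognition equations with baseline FFQ intake, the main lifestyle factors, medical conditions and medications, and indicators for family history and SCD beside APOE ε4. Keep the shorter list as a sensitivity analysis.

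Baseline diet controls confounding only as far as diet is stable, so add two more sensitivity analyses: one that also uses the FFQ collected at 12 and 24 months, and one for unmeasured mediator-outcome confounding. Describe the mediation result as observational wherever it is reported.

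The cost is a few sentences, about 6 to 10 more degrees of freedom out of about 480 for the main SEM, a slightly more complex model and some missing covariate values to handle. No new data are needed.

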## Research aims and hypothesis

2

In this study, we aim to (1) assess the longitudinal relationship between mushroom consumption and cognitive decline, measured by the absolute change in Mini Mental State Examination (MMSE) scores over a median of 10 years among surviving DaHA participants; (2) test the effects of mushroom powder (two 500 mg capsules per day) on cognitive function measured using the Symbol Digit Modality test (SDMT), the Color Trail Test (CTT) and the Rey Auditory Verbal Learning Test (RAVLT) over 12 months and 24 months, in comparison with controls who consume placebo; (3) examine the underlying protective mechanisms using biomarkers of aging (epigenetic clocks and inflammation) and measuring blood ergothioneine levels; (4) explore epigenome-wide DNA methylation changes following mushroom powder intervention and assess whether such changes correlate with cognitive and biomarker outcomes, without presupposing a beneficial direction. We hypothesized that (1) mushroom consumption will predict slower cognitive decline in a dose-dependent manner over a median 10-year period among DaHA participants; (2) daily mushroom powder consumption over 12 and 24 months will improve cognitive function (processing speed, executive function, memory) among middle-aged and young-old adults; (3) daily mushroom powder consumption will lead to favorable changes in inflammatory marker of aging that correlate with the increase in bioactive compounds from mushrooms; (4) daily mushroom powder consumption will lead to changes in DNA methylation profiles.

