We will administer the Singapore–Chinese version of the MMSE to eliminate bias from items incongruent with Singapore’s geography and culture (e.g., seasons, state/province), thereby enhancing the accuracy and sensitivity of cognitive assessment in our local Chinese population(Feng et al., 2012), in which: (1) the seasons question is replaced by “Without looking at your watch, what time is it?”; (2) the city/town question is replaced by “What area are we in?”; (3) the state/province question is replaced by “Which part of Singapore is this place (North, South, East, West or Central)?”; (4) the three-item immediate and delayed recall words are adapted to “ball, flag, tree” (English) or “柠檬, 锁匙, 气球” (Chinese); and (5) the sentence repetition item is adapted to “no ifs, ands or buts” (English) or “四十四只石狮子” (Chinese). Trained study psychologists will administer RAVLT, Color Trails Test 1&2, and both written and oral versions of the SDMT to evaluate memory, executive function and information processing speed, respectively. The above neuropsychological tests have been used in local research studies by the Principal Investigator and colleagues (Feng et al., 2006; Feng et al., 2009; Lee et al., 2012). CDR (Morris, 1993) will be administered to assess dementia severity (CDR global score). Only participants with a CDR global score of zero will be recruited. Depressive symptoms will be measured using the 15-item Geriatric Depression Scale (GDS-15)(Sheikh and Yesavage, 1986) for older participants and Patient Health Questionnaire (PHQ-9) for middle-aged participants (Kroenke et al., 2001). The PHQ-9 is a short questionnaire that measures depression severity based on the DSM-5 criteria (Kroenke et al., 2001). The GDS has been used in local studies by the principal investigator and coworkers (Feng et al., 2012; Ng et al., 2009) Dietary intake will be assessed using a Food Frequency Questionnaire (FFQ)(Whitton et al., 2017) that the trial participants will complete at baseline and follow-up visits. Information on supplements that may have neuroprotective effects, such as curcumin/turmeric, *Gingko biloba*, and polyunsaturated fatty acids, will also be collected using a questionnaire that will be designed by trial dietitian. Venous blood specimens will be collected both for the measurement of biological markers and for liver and renal panel tests for safety monitoring. To ensure consistency and minimize the influence of other factors, biological sample will be collected in the morning between 8.15 to 9.30 a.m. following an overnight fast, both at baseline and 24 months post-baseline. Table 1 provides a summary of measurements and study visits schedule.

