The level of inflammatory biomarkers and NfL in the blood will be assessed using an ELISA assays as previously described(Cheah et al., 2017). We decided to measure pro-inflammatory cytokines because both inflammatory damage has been well documented in both AD pathophysiology and the biology of aging(Querfurth and LaFerla, 2010) and the biology of aging(Franceschi et al., 2018). NfL levels have been suggested as a blood-based biomarker for neurological diseases (Fan et al., 2023). The level in plasma increases in preclinical Alzheimer’s disease (AD) before symptoms appear (Preische et al., 2019) and correlate with MCI and other AD hallmarks, such as brain shrinkage and tau tangles observed on PET scans (Raket et al., 2020). Here, we will use plasma NfL as a systemic biomarker for cognitive decline. We will generate epigenome-wide methylation data using the state-of-the-art Illumina Infinium MethylationEPIC BeadChip (Pidsley et al., 2016) on the HiScan system. The array covers over 850,000 methylation sites per sample at single-CpG site resolution, and provides unparalleled coverage of CpG islands, RefSeq genes, ENCODE open chromatin, ENCODE transcription factor binding sites, and FANTOM5 enhancers, as well as regions identified by the ENCODE project as potential enhancers. This epigenome approach will help shed light on unknown pathways and is superior to traditional approaches that focus on a limited number of genes. We will calculate epigenetic clocks using established methods and use these clocks as a quantitative measure of biological age compared with chronological age.

Furthermore, we will measure plasma ergothioneine levels using liquid chromatography-mass spectrometry at baseline, 12 months and 24 months. Correlating changes in blood ergothioneine levels with cognitive outcomes and with pathological and aging-related biological markers will shed light on ergothioneine’s mediating role in the hypothesized relationship between mushroom consumption and cognitive aging. The inclusion of biomarkers of both a mushroom-derived compound and of aging and dementia represents a novel approach not previously adopted in human studies.

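### The covariates stated for the single-CpG methylation tests include no blood cell composition, so hits and the risk score built from them could partly reflect a shift in white-cell mix

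*Protocol article*

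**What the plan says.** The methylation analysis is described in the last paragraph of Methods of analysis (3.5). It is to be "performed using a modified version of the CPACOR pipeline". After quantile normalisation, logistic regression examines the association of mushroom consumption with "each autosomal CpG site (yes/no), adjusted for age and sex". The technical adjustment follows: "Principal components from intensity values of Infinium control probes will also be included as covariates in the regression models". Then "the association results will be adjusted for the genomic control inflation factor". The sites found in this way feed a methylation risk score, using a "weighted approach (by effect size) for the CpG loci identified to be associated with mushroom consumption".

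The tissue is blood. Assessments and outcomes (3.4) says: "Venous blood specimens will be collected both for the measurement of biological markers and for liver and renal panel tests". Table 1 schedules this at baseline and 2 years. On the number of tests, the same section says: "The array covers over 850,000 methylation sites per sample at single-CpG site resolution".

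Hypothesis 3 in Research aims and hypothesis states that "daily mushroom powder consumption will lead to favorable changes in inflammatory marker of aging". Aim 4 in that section is exploratory: it looks for methylation change after the intervention and for its correlation with cognition and biomarkers, with no direction presupposed.

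No measured or estimated white-cell composition appears in the methylation paragraph, in Table 1 or in the description of the biomarkers.

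**The concern.** Venous blood is a mixture of white-cell types, and methylation at many CpG sites differs strongly between them. If one arm's mixture shifts, average methylation at those sites shifts too, even if nothing changes inside any cell. A product expected to act on inflammation could plausibly cause such a shift.

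The stated safeguards do not address this:

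- Age and sex do not capture a change caused by treatment.
- Control-probe components describe technical variation in the assay, not the biology of the sample.
- Genomic control divides all test statistics by one factor. It may dampen a widespread shift, but it cannot separate cell-mix change from within-cell change.
- Randomisation balances cell mix at baseline, but not a change that the product itself produces.

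What is at stake is interpretation. A risk score weighted by effect size could become partly a proxy for cell counts. Its correlation with inflammatory markers, which aim 4 sets out to examine, would then be partly built in.

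**Working it through.** **The plan's own figures.** The article gives no sample size or significance threshold for the methylation analysis. Its only calculation is for 24-month MMSE change: d = 0.30, two-sided alpha 0.05 and 90% power, with 235 per arm required. This reproduces: the normal approximation gives 234, and the t-based solution is 234.46, rounded up to 235. Allowing for 20% attrition, 235 / 0.80 = 293.75, so 294, which the planned 300 covers. The number per arm expected at 24 months is 300 × 0.80 = 240, and this is used below.

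**Assumed inputs, none of them in the documents.** The methylation difference between cell types at the CpG is 0.5. The between-person SD of methylation at that site is 0.02 to 0.03. The shift in one cell type is 1 or 2 percentage points. The yes/no exposure is taken to be trial arm.

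**Arm difference from cell mix alone.** Difference = shift × 0.5, and z = difference / (SD × √(2/240)), where √(2/240) = 0.0913.

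| Shift | Difference | SD 0.03 | SD 0.02 |
|---|---|---|---|
| 2 points | 0.010 | z = 3.65 | z = 5.48 |
| 1 point | 0.005 | z = 1.83 | z = 2.74 |

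**Threshold.** Bonferroni over 850,000 sites (assumed) is 0.05 / 850,000 = 5.9 × 10⁻⁸, or |z| = 5.42. Only the 5.48 cell exceeds it, and only just.

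**How large a 2-point shift is.** If within-cell variation is independent of cell mix, a site with SD 0.02 to 0.03 and a between-cell difference of 0.5 limits the SD of the cell fraction to 0.02/0.5 = 4 points up to 0.03/0.5 = 6 points. A 2-point shift is then at least 2/6 = 0.33 to 2/4 = 0.50 SD. That is larger than the d = 0.30 assumed for the primary endpoint, so it is not a small shift.

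**Chance that one cell-dependent CpG passes the threshold.** For a cell-mix shift of d SD and a CpG-to-cell-fraction correlation r, the expected z is r × d × √(240/2).

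| d | r | Expected z | Chance of passing 5.42 |
|---|---|---|---|
| 0.3 | 0.8 | 2.63 | 0.3% |
| 0.5 | 0.8 | 4.38 | 15% |
| 0.5 | 0.95 | 5.20 | 41% |
| 0.7 | 0.8 | 6.13 | 76% |
| 0.7 | 0.95 | 7.28 | 97% |

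These figures are before genomic control.

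**Does adjustment separate the two?** A simulation (2,000 runs, 240 per arm, r = 0.8, no direct methylation effect) regressed methylation on arm, as a linear stand-in for the planned logistic test. Without the cell fraction, nominal p < 0.05 occurred in about 42%, 72% and 99% of runs for shifts of 0.2, 0.3 and 0.5 SD. With the cell fraction as a covariate, it occurred in about 5% each time.

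**The case against.** Four points can be made for the plan as written.

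1. **The description is condensed.** It is flagged as brief and refers to a modified pipeline whose modification is not shown. A reader might infer that the listed covariates are the only ones. The text does not say that the list is complete, and a cell-composition step may exist in the full protocol or analysis plan. This stands, and it is why the request includes simple clarification. It does not dispose of the point, because the article chose to name its covariates and this one is not among them.

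2. **Cell mix is a mediator here, not a confounder.** A shift caused by the product is a real effect on whole-blood methylation, and the unadjusted arm difference estimates that total effect validly. Hypothesis 4 speaks only of changes in methylation profiles and never claims a within-cell effect. This stands in full. A reader might infer that aim 4 could not be interpreted without adjustment. The documents do not support that: it can be interpreted as a total effect, but the source of that effect is left open.

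3. **Nothing predicts a change in white-cell proportions.** Hypothesis 3 concerns inflammatory markers such as hs-CRP and IL-6. The step from those to cell mix is plausible, but the documents do not state it. A reader might infer that a shift would be reported as a methylation effect. The most that can be said is that it could be, and small shifts would rarely produce a hit at a single site.

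4. **The consequence is limited.** The single-CpG tests and the risk score are not among the primary or secondary endpoints named in Assessments and outcomes, and no efficacy conclusion rests on them. This is correct and keeps the point minor.

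**Conclusion.** The point holds in a limited form. The covariates stated for the single-marker tests omit blood cell composition, and nothing else in the stated analysis separates a change in cell mix from methylation change within cells. CpG associations and the risk score could therefore be partly a reading of cell counts.

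The size cannot be known from the documents. Under the assumed inputs, shifts of about 0.3 SD would seldom pass a Bonferroni threshold at one site, while shifts of 0.5 to 0.7 SD could do so with appreciable probability. This rests on the assumed between-cell difference, SD, correlation and threshold, and on there being no unstated cell-composition step in the pipeline. It is a worthwhile, low-cost improvement to an exploratory analysis, not a flaw in the trial's main comparison.

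**What to change.** Estimate cell-type proportions from the same array data. Report the single-marker results and the methylation risk score both with and without these proportions as covariates. Interpret the unadjusted result as the total effect on whole-blood methylation, and the adjusted result as the effect not acting through cell mix. The adjusted result needs the usual caution about conditioning on a post-randomisation variable. If the modified pipeline already includes this step, correct the covariate list to say so.

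The cost is a few degrees of freedom and one more set of results. No new samples, visits or assays are needed.
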